#### Reach.

We will use descriptive statistics to summarize the proportion of patients contacted who are eligible, ineligible, and agree to participate in the study. We will report the characteristics of eligible and ineligible patients by age, sex, race/ethnicity, rurality, type of primary cancer, years since cancer diagnosis and household income. These analyses are intended to identify potential trends and inform future, adequately powered studies rather than to test hypotheses.

#### Implementation.

We will use descriptive statistics to summarize participant engagement, completion of activities and attendance in sessions and then explore if these co-variates are associated with clinical outcomes. Adequate demonstration of engagement/retention in the intervention and study will be demonstrated if at least 70% of participants complete six of the nine intervention sessions, and if at least 90% of participants complete all data collection points [66]. Furthermore, we will use Fisher’s exact test to explore if there are differences in adherence/completion of the intervention based on age, sex, race/ethnicity, rurality, type of primary cancer, years since cancer diagnosis and household income. We will use descriptive statistics to summarize the fidelity to checklists completed by study interventionist as well as fidelity to protocol training.

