Multiple efficacious interventions exist for loneliness. A meta-analysis of interventions found efficacy in reducing loneliness through interventions that improved social skills, enhanced social support, and increased opportunities for social contact [27]. Building from the evidence and recognizing the substantial problem of loneliness on health, the 21st U.S. Surgeon General, [name], published an advisory on the loneliness epidemic that highlights three vital components of social connection: structure, function and quality [1,2]. Structure refers to the type, number and variety of relationships; function refers to the ways in which relationships serve an individual’s various needs (e.g., emotional, social and/or spiritual); and quality refers to the positive and negative aspects of relationships and interactions and how it is perceived by the individual. This model is adapted from Holt-Lunstad’s framework for understanding why social relationships are important for mental and physical health [28]. Social prescribing is a United Kingdom-based model to address loneliness [29]. In social prescribing interventions, patients are referred by general practitioners and then partner with lay and/or peer workers to develop personalized strategies to improve support and connection [30–35]. While evidence supports its’ efficacy, social prescribing has not been applied widely outside the United Kingdom and Europe [34,35]. Furthermore, it has not been tested specifically for adult cancer survivors with loneliness.

The aim of this study is to conduct a feasibility pilot randomized controlled trial to test, in adult cancer survivors who receive care in rural and rural-serving primary care practices, a loneliness intervention that draws on the principles of social prescribing. We will enroll 36 adult cancer survivors who are experiencing loneliness, and who will be randomized to either Enhanced Social Prescribing (n = 18) or usual care (n = 18). We will collect outcomes on loneliness, social connection, self-efficacy, quality of life, and quality of cancer survivorship care. Our goal is to improve overall wellness and quality of life among cancer survivors and demonstrate pilot efficacy of a novel, adapted program that may improve survivorship care outcomes.

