## Outcomes

### Assessment of trial feasibility

#### Research procedures feasibility.

Research procedures feasibility outcomes include number of individuals screened, number of individuals enrolled, time to first enrollment, time to reach enrollment milestones (25% target enrollment, 50% target enrollment, 75% target enrollment, 100% target enrollment), completeness of baseline and follow-up data, rate of participant drop-out or withdrawal, and the proportions of participants randomized to enhanced social prescribing that attended each scheduled session. Progression criteria for feasibility assessment are shown in Table 1.

**Table 1 pone.0350956.t001:** Progression criteria for feasibility assessment.

	Green	Yellow	Red
50% Enrollment	3 months	6 months	9 + months
Baseline data collection	100%	90%	50% or less
Drop out	<1	1-2 participants	N/A*
Intervention delivery	75% of participants	60% of participants	<60% of participants

• If greater than 2 participant drop outs are noted during the course of the study, the team will undertake full review of the study protocol and procedures to identify and mitigate design features that may be contributing to drop out.

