## Discussion

### Expected findings

We anticipate successful recruitment of 36 adult cancer survivors with loneliness, delivery of the Enhanced Social Prescribing intervention to 18 participants and delivery of enhanced usual care to 18 participants. We anticipate high study retention, with at least 70% of participants will completing all data collection and high intervention engagement with at least 70% of participants assigned to the intervention attending at least 2/3 of the intervention visits. This feasibility study will demonstrate the feasibility of conducting a larger-scale randomized controlled trial to test the effectiveness and study the implementation of the Enhanced Social Prescribing intervention. While not powered for statistical significance, we also anticipate that the Enhanced Social Prescribing intervention will lead to reduced loneliness among adult cancer survivors as measured by the UCLA Loneliness Scale.

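### The feasibility thresholds are inconsistent: full data completion is 90% in one section and 70% in another, and Table 1 grades drop-out and delivery without being tied to either

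*Protocol article*

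**What the plan says.** Three places in the protocol article bear on retention and attendance.

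- **Statistical analyses, Implementation.** Engagement and retention are adequate if "at least 70% of participants complete six of the nine intervention sessions, and if at least 90% of participants complete all data collection points".
- **Discussion, Expected findings.** The authors anticipate high retention, "with at least 70% of participants will completing all data collection", and at least 70% of the intervention arm attending two thirds or more of the visits.
- **Table 1, progression criteria (Research procedures feasibility).** Drop-out is green below one, yellow at "1-2 participants", and not applicable for red. The footnote adds: "If greater than 2 participant drop outs are noted during the course of the study, the team will undertake full review". Intervention delivery is green at "75% of participants", yellow at 60% and red at "<60% of participants". No number of sessions is attached to delivery.

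No section says how Table 1 relates to the Implementation criterion, or which prevails if they differ.

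**The concern.** The Feasibility paragraph of the statistical analyses makes assessing feasibility a primary goal. The sample size section states that no calculation was done. The feasibility thresholds are therefore the main standard set in advance for judging the study.

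Two sections give different figures for one measure. The table of progression criteria uses other measures, which are neither defined nor linked to that figure. Unless this is settled beforehand, the team will have to decide after seeing the counts how the criteria fit together.

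**Working it through.** The plan gives no calculation behind these thresholds, so there is no figure to reproduce. The check turns each percentage into a count and compares the labels.

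**Inputs.** Introduction: "We will enroll 36 adult cancer survivors who are experiencing loneliness", with 18 per arm. Thresholds are as set out above. The retention denominator is taken as all 36 and the attendance denominator as the 18 assigned to the intervention.

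**Data completion, same measure in two sections**

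- Implementation: 0.90 × 36 = 32.4, so at least 33 completers and at most 3 lost.
- Expected findings: 0.70 × 36 = 25.2, so at least 26 completers and at most 10 lost.
- From 26 to 32 completers (72.2% to 88.9%) the forecast of high retention is met and the adequacy criterion is failed.

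**Drop-out in Table 1 against data completion.** This table assumes that each drop-out fails to complete all data points and that everyone else completes them.

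| Drop-outs | Completers | Table 1 | Implementation | Expected findings |
|---|---|---|---|---|
| 0 | 36 (100%) | green | adequate | met |
| 1–2 | 35–34 (97.2%–94.4%) | yellow | adequate | met |
| 3 | 33 (91.7%) | full review | adequate | met |
| 4–10 | 32–26 (88.9%–72.2%) | full review | not adequate | met |
| 11 | 25 (69.4%) | full review | not adequate | not met |

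**How often the review would be triggered.** Under the same assumption, and with independent losses at a true rate p, the number lost is Binomial(36, p). The documents give no expected loss rate, so p is assumed. At p = 0.10:

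- P(0) = 0.9^36 = 0.0225
- P(1) = 36 × 0.1 × 0.9^35 = 0.0901
- P(2) = 630 × 0.01 × 0.9^34 = 0.1752
- P(more than 2) = 1 − 0.2879 = 0.71

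| Assumed loss | P(more than 2 lost) | P(at least 33 complete) | P(exactly 3 lost) |
|---|---|---|---|
| 5% | 0.27 | 0.90 | 0.16 |
| 10% | 0.71 | 0.51 | 0.22 |
| 30% | above 0.999 | 0.002 | 0.001 |

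The last column is the chance of the direct clash, in which retention is adequate and a review is also triggered.

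**Attendance**

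- Two thirds of nine sessions is 6, so Implementation and Expected findings use the same rule. 0.70 × 18 = 12.6, so at least 13.
- Table 1 green: 0.75 × 18 = 13.5, so at least 14. Table 1 yellow: 0.60 × 18 = 10.8, so at least 11, reading everything from 60% up to 75% as yellow.
- If delivery means attending six of nine sessions, 13/18 (72.2%) is adequate under Implementation and yellow in Table 1. Counts of 11 and 12 (61.1% and 66.7%) are yellow and not adequate. From 14 upwards the two agree on success, and at 10 or fewer they agree on failure.

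**The case against.** The strongest reply is that these are not rival rules.

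- **Expected findings is a forecast.** It says what the authors anticipate and decides nothing. This stands. A reader might infer three competing success rules and a free choice among them, but nothing in the article lets the team declare success at 26 of 36. What remains is that the forecast calls high a level that the article's own criterion would fail.
- **Drop-out and data completeness are listed as separate feasibility outcomes.** A participant can miss a survey without dropping out. This also stands, and it is why the side-by-side table and the 0.71 are conditional. It does not remove the clash at three drop-outs when all others complete, and the article does not define drop-out or link the two measures.
- **The footnote prompts a review during the study and is not a verdict of failure.** Correct. A mid-study review and an adequate final result can coexist. However, the footnote takes the place of a red band in a table of progression criteria, and its effect on the progression decision is not stated.
- **A 70% minimum can lie inside a yellow band.** This is possible, and the disagreement over success concerns a single count, 13/18. The delivery measure may also be defined in the approved protocol supplement, which is not shown. A missing definition alone would be no finding. The differing percentages in the article are.

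A reader might also infer that one retention result can be adequate, borderline and a review trigger all at once. The table above shows that no count receives all three labels.

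**Conclusion.** The thresholds are inconsistent and should be reconciled. The clearest part is 90% against 70% on one measure, which leaves 26 to 32 completers meeting the forecast and failing the criterion. Next is the unexplained relation between the drop-out grading and the 90% criterion: three drop-outs with all others complete gives 91.7%, which is adequate, and a full review. The 0.71 chance of triggering that review rests on an assumed 10% loss with every loss counted as a drop-out; it falls to 0.27 at 5%. The attendance mismatch is small. It lies only between Table 1 and Implementation and changes the success verdict at one count.

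This is a should-fix point. It does not touch randomization, outcome estimates or safety, and because feasibility results are to be reported descriptively, readers can see the raw counts. It matters because it leaves the standard for a primary goal of the study unsettled.

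**What to change.** Before outcome data are reviewed, make Table 1 the single set of progression criteria and have the other sections refer to it.

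1. **Data completion.** Add a row for completing all data collection points among all 36 randomized, with the 90% from Implementation (33 of 36) as the success level. Correct Expected findings to match. The forecast's 70% should not become a lower band by default.
2. **Drop-out.** Keep it as a separate row and define it. State that more than two triggers a review, and how that bears on the progression verdict.
3. **Intervention delivery.** Define it as attending at least six of nine sessions among all randomized to the intervention. Choose one success percentage, 70% (13 of 18) or 75% (14 of 18), and use it in both Table 1 and Implementation, with contiguous bands so that every count has one label.

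The cost is wording plus a protocol modification submitted for ethics review, which the Trial governance section already provides for. Recruitment opened on 15/03/2026 and data collection is expected to end by 12/31/26. The change should be dated, so that it is clear that it came before the outcome data were reviewed.

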#### Appropriateness and acceptability.

We will use descriptive statistics to summarize the acceptability and appropriateness of the intervention using the AIM and IAM measures with intervention participants. Feasibility will be explored qualitatively in interviews with the connection navigator and primary care clinical partners.

### Data management and storage

All quantitative data will be collected and stored in REDCap [67,68], hosted by the Institute of Translational Health Sciences at the University of Washington. Data cleaning, coding, and analysis will be conducted in Stata Version 19 (College Station, TX). Detailed coding files, data dictionaries and analysis programming will be stored in a secure file on the University of Washington SharePoint server. Final de-identified datasets and associated data dictionaries will be uploaded to an appropriate data repository, discoverable via persistent unique identifier. Access will be granted upon appropriate request. All data management activities will be compliant with federal, state, and local regulations and institutional human subjects division protections. No data monitoring committee is indicated for this small, feasibility study.

### Anticipated risks and benefits

Enhanced Social Prescribing may reduce loneliness and improve social connection among intervention participants. Enhanced usual care may reduce loneliness and improve social connection among participants receiving it. We will gather information from usual care participants to determine if and how they sought social support to assess this potential. Some psychological distress may result from the Enhanced Social Prescribing intervention since participants will be discussing their experiences with loneliness in the context of how to overcome loneliness. When psychological distress occurs, the study interventionist will try to address this in the context of the current session. If this is ongoing by the end of the session, the participant will be referred to resources as additional supports to address this psychological distress. If exacerbated psychological distress occurs (including suicidal ideation), the study interventionist will immediately attempt to contact the patient’s primary care clinician. If they are unavailable, the interventionist will contact one of the clinician investigators (Drs. [name] or [name]) who will assess the patient and make appropriate referrals for immediate care, including the possibility of referring the patient to the national crisis lifeline or advising them to care immediately in the emergency department.

Adverse events will be reported in accordance with local, state, and federal regulations and University of Washington Human Subjects Division policies.

### Criteria for discontinuation

The trial will be discontinued if safety monitoring identifies an unacceptable level of psychological distress among participants as defined a priori using a validated measurement instrument (e.g., PHQ-9) and reviewed by the research team.

**Patient and public involvement** – We conducted key informant interviews with patient partners and clinical staff (e.g., psychologists, social workers, oncologists) that work with cancer survivors to design the enhanced social navigation intervention and outcomes assessment. Patient partners will remain involved as key advisors throughout the project and contribute to interpretation of our results and dissemination.

### Trial governance

All scientific and programmatic decisions are made by the principal investigator and do not represent the views of the funders. This study was reviewed and approved by the University of Washington Human Subjects Division (IRB ID: STUDY00023577). Protocol updates and modifications will be submitted for review to the UWHSD.

### Dissemination

We plan to disseminate our findings in journals and at cancer control/survivorship, behavioral health, and primary care health national conferences. We will also develop a 1-page summary to disseminate the results of the study back to participating clinics and community organizations, and to other interested clinics within the WWAMI region Practice and Research Network. Demonstration of a pilot efficacy and feasibility of the Enhanced Social Prescribing intervention is essential for development of a future type 1 hybrid effectiveness-implementation trial that tests the Enhanced Social Prescribing intervention for cancer survivors with loneliness on a larger scale. The Enhanced Social Prescribing intervention has the potential to have substantial impact by reducing loneliness in a high-risk population (adult cancer survivors with loneliness) who already face substantial physical and mental health disparities. This proposal not only advances care for adult cancer survivors but also has the potential to have substantial impact in building community-clinical partnerships to address other disparities and improve overall community health and mind-body-spirit well-being.

## Discussion

### Expected findings

We anticipate successful recruitment of 36 adult cancer survivors with loneliness, delivery of the Enhanced Social Prescribing intervention to 18 participants and delivery of enhanced usual care to 18 participants. We anticipate high study retention, with at least 70% of participants will completing all data collection and high intervention engagement with at least 70% of participants assigned to the intervention attending at least 2/3 of the intervention visits. This feasibility study will demonstrate the feasibility of conducting a larger-scale randomized controlled trial to test the effectiveness and study the implementation of the Enhanced Social Prescribing intervention. While not powered for statistical significance, we also anticipate that the Enhanced Social Prescribing intervention will lead to reduced loneliness among adult cancer survivors as measured by the UCLA Loneliness Scale.

### Limitations

Several limitations exist. First, participant sample bias might occur, since the participants who agree to participate in this study may be more motivated to address loneliness than the general population. However, this is likely to bias us toward the null, given our plan for randomization. Second, this feasibility study is not intended to establish effectiveness of the intervention, and sub-group analyses are not possible with this small sample.

## Conclusions

Loneliness in cancer survivors affects well-being, health outcomes and concordance with guideline recommended care. Cancer survivors have specialized needs for addressing loneliness given unique contributors to loneliness and life experiences in this population. To our knowledge, our study is the first to explore using an adapted social prescribing intervention to address loneliness in cancer survivors and has the potential to substantially improve the health and well-being of cancer survivors.
